### Interim analyses {21b}

There are no plans for any interim analyses because the safety and effectiveness of the HAP intervention has been demonstrated in a previous trial.

### Methods for additional analyses (e.g. subgroup analyses) {20b}

#### Mediation

We will conduct mediation analysis using the Monte Carlo Method for Assessing Mediation (MCMAM) to assess the effects of quantitatively measured a priori mediators on primary outcomes [34]. MCMAM performs better than the Sobel test and comparably with bootstrapping approaches [35]. After examining individual mediation pathways using MCMAM, we will conduct a multiple mediation model examining all significant mediation pathways using structural equation modelling (SEM). All analyses will adjust for relevant baseline variables as well as potential covariates, including patient-, counsellor-, and treatment-level characteristics [36].

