### Objectives {7}

Through the IMPRESS (*IMP*lementation of evidence based facility and community interventions to reduce the treatment gap for dep*RESS*ion) programme, we aim to increase both the contact coverage and effective coverage of a scaled-up, evidence-based psychosocial treatment for depression (Healthy Activity Program-HAP) [9] and, in doing so, reduce the treatment gap for depression in a cost-effective manner. We will do this by examining if the addition of a community intervention (Community Model) delivered by community volunteers enhances the population-level impact of scaled-up HAP in routine primary care (Facility Model) by increasing demand for HAP and improving HAP adherence and effectiveness. We will conduct an economic evaluation, to estimate the cost-effectiveness of the Community Model in comparison to the Facility Model, and use the estimates of the cost of the delivery of the interventions to model the financial sustainability of scaling it up across India.

Our
*primary hypotheses* are that the Community Model will be superior to the Facility Model in reducing the treatment gap for depression through

(1a) Increasing the demand for depression treatment in primary care (contact coverage outcome); and(1b) Reducing depressive symptoms at three months post-recruitment amongst those who screen positive for moderately severe and severe depression (effectiveness outcome)

(2)Our *secondary hypotheses* are that the Community Model will be superior to the Facility Model in

(2a) Achieving a sustained reduction in symptoms of depression;(2b) Increasing short-term and sustained remission from depression;(2c) Achieving a greater response to HAP;(2d) Increasing perceived social support;(2e) Achieving higher treatment completion rates; and(2f) Increasing patient-reported activation levels.

In addition, we also hypothesize that the Community Model will increase community awareness about depression.

(3)Finally, we hypothesise that the superior outcomes of the Community Model will be mediated through:

(3a) Increased community awareness about depression (for contact coverage);(3b) Greater perceived social support (for effective coverage);(3c) Higher treatment completion rates (for effective coverage); and(3d) Increased patient-reported activation levels (for effective coverage).

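### The joint mediation model admits only pathways that are significant one at a time, which for weak to moderate pathways drops true mediators and inflates the ones kept

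*Protocol article*

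**What the plan says.** Objectives {7} lists the mediation hypotheses under the statement "we hypothesise that the superior outcomes of the Community Model will be mediated through". One mediator, community awareness (3a), is tied to contact coverage. Three are tied to effective coverage: perceived social support (3b), treatment completion (3c) and patient-reported activation (3d).

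The Mediation section under {20b} uses the Monte Carlo method (MCMAM) "to assess the effects of quantitatively measured a priori mediators on primary outcomes". The second step follows in a fixed order: "After examining individual mediation pathways using MCMAM", "we will conduct a multiple mediation model examining all significant mediation pathways using structural equation modelling".

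The article names no separate data for the second step and no correction for the selection. Nothing elsewhere in it says that all hypothesised mediators enter the joint model.

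**The concern.** With three mediators named in advance there is no need to reduce their number, yet the data decide which of them receive a jointly adjusted estimate. Two biases follow.

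- **Selection.** A pathway enters because its estimate was large enough to be significant, and it is then re-estimated on the same participants. Its expected value, given entry, lies further from zero than the truth.
- **Absorption.** If a true mediator is screened out and is correlated with one that stays, the retained mediator picks up part of its effect. Correlation is plausible here: in the Community Model the same volunteers are meant to encourage activation, support homework and follow-up, and involve the family.

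At stake is how effect is apportioned between support, completion and activation in the joint model. The rule has nothing to act on for contact coverage, which has one mediator.

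**Working it through.** **Inputs from the article (Sample size {14}, Trial design {8}).** 28 clusters, 14 per arm; 17 analysed per cluster; 28 × 17 = 476; PHQ-9 means 11.9 (SD 7.0) and 8.9 (SD 7.2); coefficient of variation 0.2; 5% level, taken as two-sided.

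**The plan's own figure first.** The mediation section states no figure, so the check is on the power of the sample in which the three-mediator model would be fitted. Cluster-trial formula: power = Φ(√[(c − 1)d² / ((s₀² + s₁²)/m + k²(μ₀² + μ₁²))] − 1.96).
- (49 + 51.84)/17 = 5.93
- 0.04 × (141.61 + 79.21) = 8.83
- √(13 × 9 / 14.76) = 2.815, and Φ(0.855) = 80.4%

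The stated 80% is reproduced.

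**Assumptions (not in the article).** Standardised paths a (arm to mediator) and b (mediator to outcome), equal across mediators within a scenario; mediator correlation 0.4 unless stated; ICC 0 or 0.05; all three mediators treated as continuous.

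**Selection by hand.** The arm-to-mediator path is the bottleneck because arm varies only between clusters.
- SE(a) = √(4/476 × DE), with DE = 1 + 16 × 0.05 = 1.8, so SE = 0.123. Without clustering it is 0.092.
- Probability of passing on the a path is about Φ(a/SE − 1.96). For a = 0.2, 0.3, 0.4 and 0.6 with ICC 0.05 this is 37%, 68%, 90% and 99.8%.
- The mean of the estimate given that it passes is a + SE × φ(h)/(1 − Φ(h)), with h = 1.96 − a/SE. Divided by a, this gives 1.63, 1.21, 1.06 and 1.00.

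**Absorption by hand.** With equal b and equal correlation r = 0.4 given arm, the coefficient of a retained mediator is b(1 + 2r) = 1.8b if it is alone in the model, b(1 + r/(1 + r)) = 1.29b if two are in, and b if all three are in.

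**Simulation.** Each mediator was tested alone with a Monte Carlo 95% interval for a × b; those that passed were refitted jointly on the same data. For ICC 0.05:

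| a / b | True indirect effect | Each true pathway dropped (r = 0 to 0.5) | All three kept (r = 0.3 to 0.5) | Inflation of kept effects (r = 0.4) |
|---|---|---|---|---|
| 0.2 / 0.2 | 0.04 | 60–65% | 12–17% | about 2.1 |
| 0.3 / 0.3 | 0.09 | 29–32% | 42–47% | about 1.4 |
| 0.4 / 0.3 | 0.12 | 8–11% | 77–79% | about 1.1 |
| 0.6 / 0.3 | 0.18 | about 0% | 99–100% | nil |

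The drop rates agree with the hand figures. With uncorrelated mediators, where only selection acts, simulated inflation at 0.2/0.2 and 0.3/0.3 is about 1.6 and 1.2, also as the hand formula gives.

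Without clustering, at a = b = 0.2 and r = 0.4, repeated runs kept all three mediators in 30–34% of trials and none in 13–15%. The mean kept effect was 0.061–0.062 against a true 0.040, about 1.55-fold at the upper figure. At 0.3/0.3 inflation was about 9%, and at 0.4/0.3 about nil.

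**Coverage of 95% intervals for kept effects.** About 95% at a = b = 0.2 without clustering. With ICC 0.05 and correlated mediators it falls to 87–90% at a = b = 0.2 (about 88% at r = 0.4) and is 94–97% at the stronger paths. One further low figure, 87%, arose for a mediator with b = 0 correlated 0.5 with two true ones. That mediator passed the one-at-a-time screen in about 90% of trials.

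**All three entered regardless.** Mean indirect effects stay within about 0.002 of the truth in every scenario, with coverage of 93–96%.

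**The case against.** **The size rests on unknown paths.** This stands. The planned SMD of 0.4 gives a rough yardstick. Three indirect effects of 0.04 total 0.12, or 30% of it; three of 0.12 total 0.36, or 90%. If these pathways carry most of the planned effect, the bias is only about 1.1-fold. Against that, the scenario with no bias needs 3 × 0.18 = 0.54, more than the whole planned effect.

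**A reader might infer that the joint model's estimates and intervals become invalid altogether.** The material does not support that. Without clustering, coverage stays near 95% even for weak paths, and bias fades as paths strengthen.

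**A reader might also infer that screened-out mediators vanish from the results.** The article does not say so. Every mediator is first examined alone by MCMAM, and nothing suggests that those results will be withheld. What is lost is the jointly adjusted estimate.

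**The simulation favours the remedy.** The data came from a parallel three-mediator model, so fitting that model must recover the truth. The real mediators may act in sequence, and completion is categorical. This is fair, but a wrong ordering would affect the plan's own joint model equally, so it does not defend the screen.

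**This could be left to the analysis plan.** A detailed plan is still to be agreed before analysis. But the article states the rule, and an analysis plan that follows it would carry the bias.

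**Conclusion.** The point holds, within limits. The article fixes a significance gate into the joint mediation model for three mediators that it had already named. For weak to moderate pathways the gate drops true mediators and overstates the rest; for strong pathways it does little or nothing. The range of about 2.1-fold down to nil rests on assumed path strengths, a mediator correlation of 0.4, an ICC of 0.05 and continuous mediators, none of which the article gives. Loss of interval coverage is a lesser issue, confined to weak or null paths with clustering. The matter concerns an additional analysis of effective coverage only. The primary and secondary arm comparisons and the sample size are not affected. It should be corrected, but it does not threaten the trial's main conclusions.

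**What to change.** In the Mediation section, or in the analysis plan before any analysis, replace the screen with one joint model for effective coverage that contains social support, treatment completion and activation whatever their single-mediator significance. State the assumed ordering of the three mediators and allow for clustering by health-centre cluster. Report every indirect effect with its interval, next to the single-mediator MCMAM results for all mediators.

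The cost is a sentence or two of wording, with no new data and no change in sample size. The one downside is slightly wider intervals than a reduced model would give.

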#### Qualitative

A thematic analysis approach will be used to analyse qualitative data [37]. The themes used for the interviews and group discussions will provide the a priori framework for mixed inductive-deductive coding of the data. All FGDs and IDIs will be audio-taped; the recorded interviews will be transcribed verbatim and local language interviews will be translated into English. Subsequently, the memos (reflective notes about the interviews) and field notes written by the interviewers will be attached to the main text of the interviews. Data collection and analysis will progress iteratively, identifying and interpreting themes, leading to modifications to the interview and group discussion guides. Coding will involve grouping participants’ responses into categories that bring together similar ideas, concepts, or themes. Patterns will be derived by comparing responses to themes and examining how themes are interacting with each other.

### Methods in analysis to handle protocol non-adherence and any statistical methods to handle missing data {20c}

Outcome and covariate data will be investigated for missingness, and multiple imputation methods will be considered.

### Plans to give access to the full protocol, participant-level data, and statistical code {31c}

The full protocol is available on ClinicalTrials.gov (ID NCT05890222). One year after unmasking and completion of analyses of both 3- and 6-month outcome data (whichever is earlier), the trial dataset will be stored in a publicly available repository. The stored dataset will only have anonymised participant data.

## Oversight and monitoring

### Composition of the coordinating centre and trial steering committee {5d}

Two committees will monitor the progress of the trial (Table 5). Summary statistics and graphs showing trends over time will be compiled for the process indicators and reported on a three-monthly basis to the trial steering committee.

**Table 5 Tab5:** Trial management committees

**Committee**	**Role**	**Members**	**Frequency of meetings**
Trial management committee (TMC)	• Monitor all aspects of the conduct and progress of the trial • Ensure that the protocol is adhered to • Take appropriate action to safeguard participants and the quality of the trial	• Lead principal investigator • Programme director • Intervention team leaders • Project coordinators • Data manager	Fortnightly
Trial steering committee (TSC)	• Overall supervision of the trial • Approval of trial protocol and any protocol amendments • Ensure compliance with protocol • Final decisions about continuation or termination of the trial or substantial amendments to the protocol	• Principal investigators (chairperson) • Co-investigators • Programme director • Intervention team leaders • Project coordinators	Three-monthly

### Composition of the data monitoring committee, its role and reporting structure {21a}

The data safety monitoring board (DSMB) will meet before the start of the trial and at 6 monthly intervals. It will be independent of the sponsor and competing interests. It will review the accruing trial SAE reports, determine whether there are any safety issues that should be brought to participants’ attention, determine if there are any reasons for the trial not to continue or pause, and make recommendations to unblind data and make further recommendations to the TSC. It comprises of a psychiatrist with expertise in community trials ([name]), a public health expert with expertise in community interventions ([name]), a bioethicist ([name]), and a biostatistician ([name]).

### Adverse event reporting and harms {22}

We expect serious adverse events (SAEs) to be reported by the participant, observed by the counsellors and/or *Sangathi* during intervention delivery and by outcome assessors during the 3- and 6-month outcome evaluation. The following serious adverse events (SAEs) will be reported to the DSMB and IRBs as per their guidelines: unplanned hospitalisation, attempted suicide, victimisation (violence against the trial participant), and death by any cause, including suicide. The report will also be shared with a clinician independent of the trial. The independent clinician will contact the participant to complete a detailed interview to determine any association with trial interventions and recommend any necessary intervention. No stopping rules are proposed because SAEs are not expected to result in the trial as the HAP intervention is not experimental or associated with SAEs.

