### Intervention description {11a}

#### Facility model

The HAP, a manualised and evidence-based psychosocial treatment based on behavioural activation [9, 15, 16], will be delivered by the trained counsellors. HAP includes the following strategies: psychoeducation, behavioural assessment, activity monitoring, activity structuring and scheduling, activation of social networks, and problem-solving. Homework is assigned between sessions. HAP will be delivered in an individual format. It entails three phases of treatment, delivered over a maximum of six to eight weekly sessions, each lasting up to 40 min. Sessions will be delivered face-to-face, at the health centre where the counsellors are already employed.

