#### Community model

In addition to the Facility Model, village clusters in this arm will receive a community intervention delivered by the *Sangathis* to (i) enhance demand for the HAP treatment and (ii) promote engagement with, and completion of, the HAP treatment. The community intervention is co-produced through a rigorous intervention development process, with local community members, and includes strategies such as activities to increase awareness about depression (e.g. organising community meetings and street plays) and dissemination of psycho-educational materials (e.g. leaflets and posters), identification of people with possible depression in the community, and facilitation of access to HAP (e.g. accompanying them to the health centre for counselling sessions). Additionally, the *Sangathis* will coordinate continuing care of people receiving HAP, through home visits to encourage behavioural activation, homework completion and following up with the patient, and engaging family members to support the patient in achieving treatment goals.

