### Implementation {16c}

The enrolment of participants will be done by case managers. All consenting participants in the Facility Model will receive HAP, and those in the Community Model will receive support from the *Sangathi* in addition to the HAP.

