## Data collection and management

### Plans for assessment and collection of outcomes {18a}

The individual level effectiveness outcomes will be assessed at the participants’ homes, any other convenient location, or over the phone by a team of researchers independent of the intervention team and blind to the allocation status of the participant. The primary endpoint assessment will occur within 4 weeks of the 3-month endline date and similarly for the 6-month endline. The qualitative data will be collected by a team of researchers which is independent from the outcome evaluation team and treatment providers.

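### An all-source SAE count by arm is open to unequal ascertainment, because Sangathis observe SAEs in the Community Model only

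*Protocol article*

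**What the plan says.** The section Adverse event reporting and harms {22} names four sources of SAEs. Three come first: "We expect serious adverse events (SAEs) to be reported by the participant, observed by the counsellors and/or *Sangathi* during intervention delivery". The sentence then adds a fourth: "by outcome assessors during the 3- and 6-month outcome evaluation". The SAEs to be reported are unplanned hospitalisation, attempted suicide, victimisation, and death by any cause.

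The Sangathi source belongs to one arm. Table 1 lists Sangathis under the Community Model only, and Implementation {16c} says that "those in the Community Model will receive support from the *Sangathi* in addition to the HAP". Under Community model, they coordinate continuing care "through home visits to encourage behavioural activation, homework completion and following up with the patient", and they engage family members. Who will be blinded {17a} lists them as unblinded.

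The outcome assessors work in both arms. Section {18a} says the effectiveness outcomes are assessed "by a team of researchers independent of the intervention team and blind to the allocation status of the participant".

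The data safety monitoring board (section {21a}) reviews accruing SAE reports and considers whether the trial should continue or pause. No stopping rules are proposed. The article specifies no between-arm SAE comparison and does not say which source such a comparison would use.

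**The concern.** Both arms receive HAP, so what is randomised is the community intervention. Evidence on whether that intervention causes harm comes from the contrast between arms. One of the observers who feed the SAE record exists only because of the randomised intervention. Sangathis visit homes and talk to families, so they are well placed to hear of violence, a suicide attempt, an admission or a death that would otherwise go unrecorded.

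If all reports are pooled, the arm with the extra observer should record more events even when true risk is the same. An excess in the Community Model could then be harm, better detection, or both. Unless the source of each report is kept, neither the board during the trial nor the authors at the end could separate these. The source and a standard question have to be captured when data are collected. A later analysis plan cannot recover them.

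**Working it through.** The documents state no SAE rate and no detection rate, so there is no figure to reproduce. The check has two parts.

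**1. Which sources are common to both arms**

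| Source | Facility Model | Community Model | Blinded |
|---|---|---|---|
| Participant report | yes | yes | no |
| Counsellor, during HAP | yes | yes | no |
| Sangathi, during home visits and follow-up | no | yes | no |
| Outcome assessor, 3 and 6 months | yes | yes | yes |

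The third row is the only one that differs by arm as a matter of design.

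**2. How much this could matter (illustration with assumed rates)**

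Let *c* be the probability that an SAE is found through the routes common to both arms. Let *s* be the probability that Sangathi contact finds an SAE that those routes miss. With equal true risk:

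observed ratio (Community / Facility) = [c + s(1 − c)] / c

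Both *c* and *s* are assumptions.

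| c | s = 0.25 | s = 0.5 | s = 1 |
|---|---|---|---|
| 0.6 | 1.17 | 1.33 | 1.67 |
| 0.8 | 1.06 | 1.13 | 1.25 |
| 0.9 | 1.03 | 1.06 | 1.11 |
| 1.0 | 1.00 | 1.00 | 1.00 |

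For example, c = 0.6 and s = 0.5 give (0.6 + 0.5 × 0.4) / 0.6 = 0.8 / 0.6 = 1.33. If only assessor-collected events are compared, s = 0 and the ratio is 1.00 for any *c*.

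One cell can be tied to a figure in the article. Sample size {14} allows for 20% not followed up at 3 months. Suppose assessors find every SAE in the other 80%, nothing but a Sangathi finds SAEs in the 20%, and Sangathis find all of those. Then c = 0.8, s = 1, and the ratio is 1.0 / 0.8 = 1.25.

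In events: 28 clusters × 21 = 588 participants, and equal allocation gives 588 / 2 = 294 per arm. At an assumed true risk of 5%, there are 294 × 0.05 = 14.7 true SAEs per arm. The Facility Model records 14.7 × 0.8 = 11.8 and the Community Model 14.7, a spurious difference of about three events.

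**The case against.** The strongest objection is that the plan already contains an even-handed source. The same sentence that names Sangathis goes on to name the outcome assessors, who are blinded and see both arms on the same schedule. A reader might infer that any between-arm SAE comparison must be biased. The documents do not support that: a comparison restricted to assessor-collected SAEs is free of this problem. This part of the objection stands, and the fix builds on it.

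A reader might also infer that the Community Model has more HAP sessions by design, and so more counsellor observation. That does not follow. HAP is offered alike in both arms, "delivered over a maximum of six to eight weekly sessions, each lasting up to 40 min". The community intervention aims to "promote engagement with, and completion of, the HAP treatment", and the secondary hypothesis "2e) Achieving higher treatment completion rates" is still to be tested. Table 2 also counts meeting treatment goals or specialist referral as completion, so higher completion need not mean more sessions.

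Nor is a Facility Model participant who stops treatment out of reach. Section {11b} keeps such participants in outcome assessment unless they withdraw consent for follow-up. Section {18b} provides three contact attempts by different modalities, and self-report remains a listed source.

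Finally, no formal SAE comparison is stated, and the article leaves a detailed analysis plan to a later document. The SAE form is not shown and may already carry a source field. The absence of these details from the article is not itself a fault. What remains is what the article does state: a source confined to one arm, listed together with the others and with no order of priority among them. The independent clinician's interview about association with the interventions helps judge events that were recorded, but it cannot supply those that were never reported.

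**Conclusion.** The point holds in a limited form and is a cheap improvement. A pooled SAE count by arm is open to differential ascertainment and, under equal true risk, would be expected to lean towards more recorded SAEs in the Community Model. The direction follows from Sangathis being present in one arm only. The size cannot be obtained from the documents. The illustrative ratios of 1.00 to 1.67 rest wholly on assumed detection rates, and the effect may be small if self-report, counsellors and assessors already catch most hospitalisations, suicide attempts, victimisation and deaths.

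It would go too far to say that the data could never separate detection from harm. Assessor-collected SAEs can do much of that, provided they are asked for in the same way in both arms and kept identifiable.

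**What to change.** In Adverse event reporting and harms {22}:

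- Have the blinded assessors ask every participant they reach, in both arms, the same questions on the four listed SAE types at 3 and 6 months. The questions should cover the period since recruitment or the last assessment and come after the PHQ-9. This agrees with the existing rule in {17a} that the PHQ-9 is administered first.
- Record deaths and hospitalisations learned while tracing participants for follow-up, in the same way in both arms.
- Record the source of every SAE.
- Base any between-arm SAE comparison, for the monitoring board and the final report, on these assessor-collected events. Show all-source counts separately, broken down by source.
- Leave individual SAE reporting by counsellors and Sangathis unchanged.

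The cost is a source field on the form, a few minutes per assessment and some recall error. The assessor-based comparison will also miss events in participants lost to follow-up (20% allowed for at 3 months), and it could be affected if loss differs by arm. This is why the all-source counts should stand beside it.

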### Procedure for unblinding if needed {17b}

No procedure for unblinding is planned for this trial.

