#### Effectiveness coverage

The primary analyses will be intention-to-treat. Linear regression GEE will be used to compare mean PHQ-9 scores by arms, adjusting for within-facility clustering, baseline severity of depression and any confounding factors for which there is substantial imbalance between the arms at baseline. We will present an estimate of the effect size as an adjusted SMD and 95% confidence intervals and the intra-cluster correlation. For binary outcomes, the effect will be measured by the risk ratio (RR) and 95% confidence intervals using logistic regression models adjusted for within-facility clustering. Predefined effect-modification analyses will include adjustment for age, gender, marital status, education, employment status, and baseline PHQ-9 score. Finally, we will consider a sensitivity analysis to investigate the effect of missing data by using multiple imputation. We will not conduct an interim analysis as we do not anticipate any safety concerns related to the interventions.

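### Sangathis are a source of SAE reports in one arm only, so a comparison of SAEs by arm would be biased; and the reason given for no stopping rules or interim analysis concerns HAP, which both arms receive

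*Protocol article*

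**What the plan says.** **Sources of SAEs.** Adverse event reporting and harms {22} expects events to be reported by participants, and to be "observed by the counsellors and/or *Sangathi* during intervention delivery and by outcome assessors during the 3- and 6-month outcome evaluation". Table 1 places counsellors in both arms and Sangathis in the Community Model only.

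**Reason for no stopping rules.** The same section states "No stopping rules are proposed because SAEs are not expected to result in the trial as the HAP intervention is not experimental".

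**Reason for no interim analysis.** This is given twice. Interim analyses {21b} says none is planned "because the safety and effectiveness of the HAP intervention has been demonstrated in a previous trial". The Effectiveness coverage paragraph of the statistical methods {20a} gives a wider reason: "We will not conduct an interim analysis as we do not anticipate any safety concerns related to the interventions".

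**What differs between arms.** The sections on comparators {6b} and implementation {16c} give HAP to both arms. The Community Model adds Sangathi activities, described in {11a}: finding people with possible depression in the community, home visits, and work with families.

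**Oversight.** The data safety monitoring board (DSMB) meets six-monthly, reviews accruing SAE reports, considers whether the trial should pause or end, and may "make recommendations to unblind data and make further recommendations to the TSC" {21a}. Section {17b}, however, says "No procedure for unblinding is planned for this trial".

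**The concern.** Two things look wrong.

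First, an SAE has one more route into the record in the Community Model than in the Facility Model. The article commits to CONSORT reporting for cluster trials {20a}, so a table of SAEs by arm is to be expected. If that table pools all sources, part of any difference reflects who was watching, not what happened. The community intervention could look harmful when it is not, or a true reduction in events could be hidden.

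Second, the safety record of a treatment given in both arms says nothing about the component that is randomised. The article cites no earlier safety data for the Sangathi intervention. Its own SAE list includes victimisation and attempted suicide, and its background section names stigma as a barrier to help-seeking. An intervention that identifies people in their villages and involves their families needs a safety argument of its own.

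**Working it through.** **1. Ascertainment routes side by side** (from {22} and Table 1)

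| Source | Facility Model | Community Model |
|---|---|---|
| Participant | yes | yes |
| Counsellor | yes | yes |
| Outcome assessor, 3 and 6 months | yes, blinded | yes, blinded |
| Sangathi | no | yes |

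The counsellor route is also not guaranteed to be equal. The community intervention is meant to raise engagement with HAP and its completion {11a}. If it does, counsellors see Community Model participants more often and have more chances to learn of an event. Only the outcome assessors work to the same schedule in both arms, blind to allocation ({17a}, {18a}).

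**2. Size of the bias.** The article gives no SAE rate and no detection rate, so there is no figure to reproduce. The inputs below are assumptions.

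- d = share of true SAEs detected through the routes common to both arms, taken as equal in the two arms.
- s = share of the remaining SAEs that a Sangathi finds.

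With equal true risk, the Facility Model detects d and the Community Model detects d + s(1 − d). The apparent risk ratio is [d + s(1 − d)] / d.

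| d | s | Community Model detection | Apparent ratio |
|---|---|---|---|
| 0.90 | 0.25 | 0.90 + 0.25 × 0.10 = 0.925 | 0.925 / 0.90 = 1.03 |
| 0.90 | 0.50 | 0.90 + 0.50 × 0.10 = 0.950 | 0.950 / 0.90 = 1.06 |
| 0.70 | 0.25 | 0.70 + 0.25 × 0.30 = 0.775 | 0.775 / 0.70 = 1.11 |
| 0.70 | 0.50 | 0.70 + 0.50 × 0.30 = 0.850 | 0.850 / 0.70 = 1.21 |

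The ratio is above 1 whenever d is below 1 and s is above 0. The direction is therefore fixed by the design under these assumptions, while the size is not known.

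**3. The rationale against the design.**

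- {22} and {21b}: the reason is HAP's safety record.
- {6b} and {16c}: both arms receive HAP.
- The reason therefore concerns a background common to both arms and leaves the randomised contrast unaddressed.
- {20a}: the reason covers the interventions in the plural, which would include the Sangathi component, but no evidence is cited for that component.

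The same decision on interim analysis thus carries two different reasons, and neither is supported for the tested component.

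**4. Unblinding.** {17b} plans no procedure, while {21a} lets the DSMB recommend unblinding data. The data manager already holds the allocation ({16b}, {17a}), so the means exist. The article does not say how such a recommendation would be carried out.

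**The case against.** The strongest case on the other side is that safety is watched, and not only with HAP in mind. The DSMB is independent, includes a biostatistician and a public health expert in community interventions, and can recommend that the trial pause or end. An independent clinician interviews the participant about each SAE and judges association with the trial interventions, not with HAP alone. Section {11b} likewise refers to events possibly caused by the trial interventions. All of this stands.

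It rules out two stronger readings. A reader might infer that interim safety review is waived. It is not: only formal interim analyses and stopping rules are. A reader might also infer that harm from the community intervention is not examined by arm, or could show only as an excess between arms. The article is silent on by-arm tables, which are commonly left to a DSMB charter or full protocol not shown here, and case-by-case causality review could attribute an event to a Sangathi visit.

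On ascertainment, participant and assessor reports exist in both arms, which limits the bias, and the detection rates used above are not in the article. This also stands, and is why a range is shown. It does not remove the extra route in one arm.

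On unblinding, {17b} may concern code-breaking for care, which is unneeded when participants and counsellors know the allocation. That is a fair reading, so the gap is one of clarity, not a safety failure.

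**Conclusion.** The concern holds in two limited parts.

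- **Ascertainment.** The stated reporting route gives the Community Model one more SAE observer, so a pooled comparison by arm would be biased towards more detected events there. The apparent ratio at equal true risk is about 1.03 to 1.21 if common routes find 70% to 90% of events and Sangathis find 25% to 50% of the rest. These inputs are assumed, and the calculation takes detection by the common routes as equal between arms.
- **Rationale.** The reason in {21b} and {22} does not fit the randomised contrast and differs from the one in {20a}. This is a fault in the stated argument. It does not show that oversight is inadequate or that any particular stopping rule is needed, and none is proposed here.

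The mismatch between {17b} and {21a} is a minor point of clarity.

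**What to change.** 1. Record the source of each SAE: participant, counsellor, Sangathi or outcome assessor.
2. Base the between-arm comparison on events elicited by the blinded outcome assessors, with the same questions in both arms at 3 and 6 months.
3. List counsellor- and Sangathi-reported events separately, by arm and type, as descriptive data. All events still go to the DSMB, ethics boards and independent clinician as now.
4. Reword {21b} and {22} so that the rationale addresses the community intervention and agrees with {20a}.
5. State in {17b} how data would be unblinded if the DSMB recommends it under {21a}.

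**Cost.** A source field, a short common set of questions at visits already planned, and some wording. No extra visits or participants are needed. The downside is that events known only to counsellors or Sangathis stay out of the main comparison. That comparison also covers only participants who are followed up: the sample size section expects 17 of 21 per cluster at three months, which is 476 of 588, or 81%. The separate listing keeps the other events visible.
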